##### The Stress Reactivity Scale

The 29-item Stress Reactivity Scale measures the duration and magnitude of an effective response that a person displays in various stress situations. Each item consists mainly of 2 parts: (1) a typical stress situation and (2) 3 response items. From this, the total score can be calculated. A satisfying Cronbach α between .71 and .82 for the various subscales and good retest reliability coefficients over 7 months between .63 and .84 could be shown [86].

##### General Self-efficacy Scale

The General Self-efficacy Scale is a 10-item psychometric scale that assesses general optimistic self-conviction [87]. The items are answered on a 4-level scale (1=not correct; 2=hardly correct; 3=rather correct; and 4=exactly correct). At the end, all points are summed up, and the result is a score between 10 and 40. The internal consistency of Cronbach α is between .75 and .91. Confirmatory factor analysis could confirm the single-factor structure of the scale. The scale shows a good retest reliability of .67 [88].

##### Multidimensional Mood State Questionnaire

To assess psychological responses to acute laboratory stress induction, we will use the Multidimensional Mood State Questionnaire (German translation: *Mehrdimensionaler Befindlichkeitsfragebogen* [MDBF]) [89]. The MDBF consists of 24 adjectives that reflect positive or negative emotional states. Participants’ ratings on a 5-point Likert scale could be summed up to a total score of subjective well-being, where higher scores reflect a more positive emotional state. Sufficient reliability (Cronbach α=.80-.92) and validity of the MDBF have been confirmed in several studies [90-92]. As in previous studies by our group [50,93], we will use the MDBF at multiple time points before and after the stress tasks at T0 and T2 to assess variations in psychological well-being in response to stress (–2 minutes, +15 minutes, and +60 minutes relative to stress onset).

#### Sports Medicine Questionnaires

##### Habitual Physical Activity Questionnaire

The Habitual Physical Activity Questionnaire is divided into 3 indices evaluating (1) occupational physical activity, (2) sports, and (3) leisure time, and it originally included 16 items [94]. The German version of the Habitual Physical Activity Questionnaire was compared with the original version in 2001 and was reduced by 2 items after item-analytical analysis [95]. The test-retest reliability of the indices of physical activity over 3 months is .80 and .90 for (1) and (2) and .74 for (3) [94].

##### International Physical Activity Questionnaire (Long Version)

The long version of the International Physical Activity Questionnaire contains 27 items and collects physical activity values in different domains (occupational, transport, yard or garden, household, leisure, and sitting) and different intensities (moderate and vigorous) within the past 7 days [96]. The German long version was validated on German adolescents [97]. It is an acceptable, valid, and reliable questionnaire for assessing physical activity in many countries [96].

##### Short-Form Health Survey

The 36-item Short-Form Health Survey is a cross-disease assessment instrument for measuring the health-related quality of life of the general population and patients [98]. It consists of 8 dimensions of subjective health: physical functioning (10 questions), social functioning (2 questions), role limitations (physical problems, 4 questions; emotional problems, 3 questions), general mental health (psychological distress and well-being; 5 questions), vitality (energy and fatigue; 4 questions), bodily pain (2 questions), and general health perception (5 questions). In addition to the 8 dimensions, one question is used to request health changes [99]. These dimensions can be assigned to the functional status and well-being of the basic dimensions. The version of the Short-Form Health Survey-36 used here refers to the past 4 weeks. Except for social functioning (Cronbach α=.73), the 7 other dimensions showed acceptable internal consistency, with a Cronbach α≥.85. The test-retest reliability is excellent within 2 weeks [99].

##### Physical Activity Readiness Questionnaire

The Physical Activity Readiness Questionnaire is an internationally renowned preparticipation screening tool that was based on expert opinion (British Columbia Ministry of Health and the Multidisciplinary Board on Exercise) [100]. It intends to find whether the test participant should see a physician before beginning physical activity or a sport. Here, cardiovascular, balance, medical, emotional, and joint issues, which could hinder physical activity or sports activity, should be excluded. All questions should be answered with *no.* This questionnaire is used as an exclusion criterion in this study and is used in the telephone survey. If a question is answered with *yes,* the person is not included in the study.

### Psychological Stress Tests (T0 and T2)

#### Stress Induction Paradigms

As the study design aims to investigate acute stress effects at several time points (T0 and T2) by focusing on the change in saliva cortisol levels as a primary end point, 2 alternative paradigms for stress induction are required, which are described below. Thus, habituation and expectation effects can be reduced based on the first stress induction paradigm. These psychological stress tests will be conducted between 1:30 PM and 4 PM to control the circadian cortisol level. To eliminate possible contaminations of saliva, participants will be instructed to refrain from eating or drinking for 1 hour before the stress tests. In addition, participants will watch a relaxing movie for approximately 20 minutes to minimize baseline differences in cortisol concentrations.

#### Socially Evaluated Cold Pressure Test (T0)

Stress induction at T0 will be performed by means of the SECPT [49]. The participant will be asked to immerse their nondominant hand in a pool of cold water (0-4 °C) and to keep it there if possible. During this time, the participant will be observed by an experimenter, who will keep a neutral facial expression while taking notes on a clipboard. To further enhance the social evaluation, the face of the participant will be recorded with a mock camera. The participants will be encouraged to keep their hands immersed for a maximum of 3 minutes.

#### Psychosocial Stress Task for Scanner Environments (T2)

Stress induction at T2 will be performed using the compact version of the psychosocial stress task for scanner environments (ScanSTRESS) paradigm [50,52]. First, the participants will go through a control phase and then a stress phase (6 minutes each). During the stress phase, 2 types of cognitively challenging tasks will be processed with computer assistance (Neurobs Presentation software, Neurobehavioral Systems): mental rotation and arithmetic subtraction tasks. A preprogrammed algorithm adapts the task difficulty and speed to the participant´s performance, thus creating time pressure and forcing errors. The social-evaluative component is a jury (consisting of 2 test supervisors in white lab coats) that is transmitted via a live video stream to the screen of the participant during the task processing and thus continuously providing negative disapproving feedback. In case of too slow processing, as well as in the case of an erroneous answer, the jury can also project negative written feedback onto the respondent's screen via a buzzer (“Work faster!” and “Error!”). To further increase the stress level, the stress phase will be interrupted halfway through for verbal feedback. Here, the participant will be reminded that the data can only be used if maximum performance is achieved. Accordingly, the highest possible concentration is requested. During the control phase, the participants will only perform simple assignment tasks without time pressure and negative feedback.

#### Saliva Cortisol

To validate the effectiveness of the stress tests performed, 6 saliva samples will be collected throughout the experiment to detect the stress hormone cortisol. Commercially available Salivettes (Sarstedt) will be used for this purpose. All saliva samples will be stored at –20 °C and sent to the Institute of Biopsychology at the Technical University Dresden, Germany, for analysis. Salivary concentrations will be measured using commercially available chemiluminescence immunoassays with high sensitivity (IBL International).

### Emotion Induction and Regulation (T0 and T2)

To detect differences in the ability to regulate emotions, 2 different tests will be used in parallel to the stress tests.

#### Cognitive Emotion Regulation Task (T0)

The Cognitive Emotion Regulation Task (CERT) [101,102] comprises 3 task conditions and 2 image categories. In the first task condition, the participants are instructed to merely watch the presented stimuli and react naturally to them (*view condition*). In the second task condition, the participants are asked to cognitively modify the content of the presented image by assigning it a positive content (*cognitive reappraisal*) and thereby regulating their emotions. In the third task condition, participants are asked to indicate as fast as possible if the given mathematical equation is correct or incorrect via a button press (*distraction*). For this purpose, the participants are presented with both negative (first image category) and neutral images (second image category). The images are taken from the internationally standardized and evaluated databases *International Affective Picture System*) [103] and *Emotional Picture Set* [104]. After 1000 ms of stimulus presentation, the task instructions are presented for 1000 ms (transparent overlay). The image stimulus is then on display for another 5000 ms, followed by a 4000-ms rating phase where participants indicate their current affective state using the *Self-Assessment Manikin* scale for valence [105]. The interstimulus interval is 3000-5025 ms. In our study, the CERT comprises 75 trials of approximately 14.5 seconds each, 15 trials each for the following conditions: view_negative, view_neutral, distract_negative, distract_neutral, and reappraise_negative. In total, the CERT lasts approximately 19 minutes.

#### Script-Based Reappraisal Test (T2)

The Script-Based Reappraisal Test [106] is a computer-based behavioral experiment that assesses an individual’s ability to regulate emotions. In this experiment, text-based scripts will be presented that describe everyday situations and induce negative emotions (anger toward others, anger toward oneself, and fear). In this experiment, participants will work through several passages in which a script is first presented (20 seconds). Subsequently, participants will be instructed, depending on the passage, to reduce the emerging negative emotions within 1 minute by cognitive reassessment (reassessment passages) or to allow them to arise (control passages). At the end of each session, the participants will use *Self-Assessment Manikin* scales [105] to indicate their affective state in terms of valence and arousal (6 seconds) and type in their revaluation thoughts or negative thoughts (90 seconds). The Script-Based Reappraisal Test contains 12 revaluation sessions and 12 control sessions. At the beginning of the experiment, 2 sample runs will be performed, and the participants' questions on understanding will be answered.

### Peak Oxygen Uptake Determination (T1 and T3)

To determine the individual VO_2_peak as the primary end point and the training areas, participants will complete a stepwise incremental running test on a treadmill (Saturn, HP-Cosmos) until subjective exhaustion is reached or general indications for stopping an exercise test according to the American College of Sports Medicine guidelines are fulfilled [59]. Maximal oxygen uptake is reached if a plateau of VO_2_ is observed within the final 2 work rates of the stepwise incremental running test [59]. Here, we have untrained participants who may not be able to reach a plateau in VO_2_ uptake. Therefore, we will use VO_2_peak and take the highest value of VO_2_. To avoid outliers, there should be no high variance around this VO_2_ value within the 4 previously taken breaths. The exercise test includes a starting velocity of 4 km/hour, a duration of each step of 3 minutes, a pause time between 30 seconds and 60 seconds, and an increase in velocity by 1.5 km/hour from step to step. To determine the lactate threshold, 20 µL of whole blood will be collected from the fingertip with an end-to-end capillary (Sodium-Heparin, EKF-Diagnostics GmbH) at rest and between the stages. Heart rate (electrocardiogram), as well as oxygen uptake and carbon dioxide release (spiroergometry), will be continuously recorded. The latter will be used to estimate VO_2_peak for IG and CG at T1 and T3. VO_2_peak at T1 will be considered as innate aerobic capacity, and VO_2_peak of the IG at T3 will be considered as acquired aerobic capacity. Absolute and relative contraindications will be defined according to the American College of Sports Medicine guidelines [59].

### Infrared Thermography (T1 and T3)

Infrared thermography is a noninvasive, contact-free, nonradiating tool used to measure surface radiation temperature and patterns [107]. In this study, a high-resolution infrared camera (Jenoptik VarioCam; 480×640 pixels; focal plane array; spectral range 7.5-14 micrometers; accuracy ± 0.05 K; and set emissivity: 0.98) will be applied for the measurement of mean surface radiation temperature (*T*_sr_ [°C]) of the calves (C*T*_sr_). The infrared camera will be placed on a tripod behind the participant at the height of 85 cm. The distance between the camera and participant will be 2.30 m. The focus will be set perpendicular to the backside of the calves to capture the area from the popliteal space to the ankle. To stabilize the running position on the treadmill, a horizontal barrier made of elastic-plastic will be fixed behind the participant, and the foot position will be marked on the treadmill with adhesive tape. The infrared camera temperature scale will be set from 25 °C to 35 °C. An acclimatization period of 10 minutes will be implemented before the exercise test. The participants will only be allowed to wear ankle socks and shorts; should sleep and fast for 8 hours; should drink not more than 1.5 L of water; should be physically inactive; and should avoid cosmetics, showering, and sunbathing for at least 8 hours before the test.

We will perform 3 steps for thermogram analysis: (1) thermogram selection, (2) thermogram processing, and (3) analysis of the region of interest. We will process the image by coloring everything in black, except for the relevant area in the thermogram. This analysis procedure is in line with that of Ludwig et al [108]. The final regions of interests analysis will be performed with the software *Analysis of thermal images–TDM V2.0* (Optoprecision GmbH). The report of the entire infrared thermography procedure is in accordance with that of Moreira et al [109].

### Measurements of Blood Parameters (T1 and T3)

Before, immediately after, and 30 minutes and 60 minutes after the exercise testing, the median cubital vein will be punctured for venous blood sampling. In total, 100 mL of whole blood will be taken and further processed for the preparation of blood serum and plasma aliquots, depending on the subsequent analysis. Blood counts and physiological parameters will be assessed from the venous plasma or serum, respectively, at the defined time points. The following parameters will be included: creatine kinase, lactate dehydrogenase, hydroxybutyrate dehydrogenase, calcium, cholesterol, triglycerides, high-density lipoprotein-associated cholesterol, low-density lipoprotein-associated cholesterol, total leukocytes, erythrocytes, hemoglobin, hematocrit, mean corpuscular volume, mean corpuscular hemoglobin, platelets, neutrophils, eosinophils, basophils, monocytes, lymphocytes, and total protein. Blood plasma samples for molecular marker analysis will be aliquoted and stored at –80 °C before further processing. Venous blood will be used to determine and analyze venous cell-free DNA (concentration using quantitative real-time polymerase chain reaction [110,111]); non–disease-specific epigenetic patterns and sequence analysis using targeted next-generation sequencing [112]; endocannabinoids, catecholamines, and inflammatory lipids using mass spectrometry [113,114]; and further circulating signal transducers (extracellular vesicles and cytokines using multiplexed assays [115-117]). In parallel with venous blood sampling and additionally at each increment of the exercise test, capillary blood samples will be taken from the fingertip to determine capillary cell-free DNA concentrations.

### Lactate Threshold and Determination of the Training Ranges (T1 and T3)

On the basis of lactate kinetics during the incremental stepwise running tests, the individual anaerobic threshold (IAT) will be used to determine the intensity ranges (regeneration, light, moderate, and vigorous) for the training sessions. The IAT will be determined by means of minimum lactate equivalent +1.5 mmol/L [118,119]. Here, we will define 4 training intensities (regeneration: 50%-70%, light: 70%-85%, moderate: 85%-100%, and vigorous: 100%-110%), which are relatively related to the velocity at IAT (100%).

### Training Intervention

After the baseline examination (T0 and T1), an 8-week sports intervention will be carried out for the IG. The CG will not participate in any training interventions during this period. The training contents are interval- and continuous endurance–oriented. The external load can be individually controlled and adjusted with the help of the IAT and the related relative training intensities. The intervention is divided into 3 mesocycles and 8 microcycles (=1 week): adaptation (2 weeks), frequency (3 weeks), and intensity (3 weeks; Figure 3). One box (Training details) corresponds to a fixed training week from Monday to Sunday. 5 minutes warm up and 5 minutes cool down should be included in every training session. The numbers 1x and 2x are the weekly frequencies of the training session.

**Figure 3 figure3:**
[figure not shown]
Ideal progression of training load from eight stages over the 8-week sport intervention period. Rep: repetitions.

Here, a comprehensible protocol is used to adjust the training load using the principle of periodizing and cyclizing (frequency, intensity, time, type, volume, pattern, and progression; Figure 4) [43,45,59]. The gradual progression of the training load is based on weekly feedback of the participant via the Foster scale (0-10) [120]. The value for ailments has a higher priority than the load value. An optimal training load increase over 8 weeks of the training intervention is shown in Figure 3. After 8 weeks, each participant in the IG can end the training intervention on another stage based on the weekly feedback. In addition to the exercise training, the participants can conduct relaxation exercises in the form of stretching and mobilization exercises.

**Figure 4 figure4:**
[figure not shown]
Individual training adjustment using the modified Borg scale [120] and the FITT-VP principle [43,45,59]. FITT-VP: Frequency, Intensity, Time, Type, Volume, Pattern, and Progression.

IG and CG participants will receive a smartwatch (M430, Polar Electro Oy) to record training times and monitor daily activities (eg, step count and sitting time). In addition, smartwatch data will be used to control for additional physical activity apart from the training intervention in the IG and physical activity, in general, in the CG. Furthermore, it will be used as a mechanism to control for the effect on primary outcomes by only receiving an intervention. The heart rate and distance of the training session will be recorded by the IG using the M430, which enables comparison of the data reported via the weekly feedback with smartwatch-recorded data. In the CG, the smartwatch is only used to record daily activity. To improve adherence of all participants, 15 smartwatches will be raffled among all participants who have completed the study.

### Web-Based Supervision

The training intervention described above will be accompanied and remotely supervised with the help of a web-based physical exercise training support via a website (Figure 5) [121]. In a personal appointment after the incremental stepwise running test, the participants in the IG will be introduced to the website and will receive comprehensive information about the training. External access to the website is not possible as only study participants can register. Both the introduction and the remote training supervision will be done by 1 person, which enables the coach to supervise several participants in their training process without any time constraints. Although there is no face-to-face supervision, based on the objective training session heart rate data and GPS data as well as the subjective feedback, adequate supervision can be guaranteed remotely. Participants have the possibility to get in direct contact with the coach via a message function, for example, in case of problems or uncertainties. The weekly training schedule is also transmitted in this manner. If a participant misses the feedback, a reminder is sent via email at the beginning of the following week. In a table that participants can download from the website, they will enter various medical and sports values that are therapeutically relevant after each training session. These data will be used for evaluation and for the training adjustment of the following week, as described in Figure 4. A follow-up is planned at 12 weeks (T4) and 24 weeks (T5) after completion of T3, and participants will be asked via email to complete the web-based questionnaires used at T2.

**Figure 5 figure5:**
[figure not shown]
The home screen of the used website [121].

### Data Management and Security

All data will be recorded and stored in the Department of Sports Medicine, Prevention, and Rehabilitation (Mainz, Germany), and access will be restricted to authorized personnel. Confidential information will be stored safely in the trial files and will not be shared with any other third institution or entity except in response to a legal requirement. Electronic data will be stored on password-protected computers in a restricted-access building. All data will be pseudonymized and submitted to the evaluation team for analysis. A data manager from each department is nominated, who will be responsible for data management and processing. The data and safety management team will be formed by the members of the project. Only the data manager will have access to all personal data. Trial documentation and data will be archived for 10 years after completion of the trial. All dropouts and the reason for dropping out of the study will be reported. Any harm or unintended events during the examinations will be recorded and reported to the Landesärztekammer (State Medical Association) Rhineland-Palatinate. The results will be publicly available in open-access journals and presented via contributions at conferences and congresses according to good scientific practice.

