## Results

The study was registered in October 2019 (DRKS00018078). Enrollment began in September 2019 and was paused from April 2020 until submission of this study protocol because of the COVID-19 pandemic. Of the 161 interested people who have contacted us so far, 26.7% (43/161) fulfilled the inclusion criteria. Among the 55% (17/31) participants in the IG and 45% (14/31) participants in the CG, who completed the study (N=31), no serious adverse incidents were reported. Within the program, 9% (4/43) of participants (2/17, 12% in the IG and 2/14, 14% in the CG) withdrew because of individual reasons (dropout rate 11.4%). Approximately 19% (8/43) have not yet participated in the program because of the COVID-19 pandemic. Although the COVID-19 pandemic does not affect the web-based exercise training approach, the study had to be paused in April 2020, as it was not possible to determine the primary and secondary end points (VO_2_peak and cortisol levels) because of the lockdown of the laboratory facilities. Further study recruitment will resume when COVID-19 restrictions are completely lifted. On the basis of the experiences from the first recruitment period, the study is expected to continue for another 6 months to complete the intended sample size.

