### Strengths and Limitations

The strengths of our web-based, supervised physical exercise training approach with a focus on increasing VO_2_peak in healthy, physically inactive adults are as follows: (1) participants are not location dependent for the training sessions; (2) individualized, gradual, and timely adjustment of training content based on the individual’s feedback reduces the risk of injury, avoids overtraining, and avoids ineffective training; and (3) only 1 sports therapist or trainer is needed for training management of several training groups or trainees, which obviously has economic advantages and reduces bias from different sports therapists. However, web-based training support also has disadvantages compared with presence (face-to-face) interventions. Notably, it requires access to the internet, which limits the study population. Furthermore, we are dependent on the correct and complete documentation of the training sessions by the participants. For an objective way to control reports on the training and to remotely supervise the participants in the IG, we included a smartwatch (Polar M430) that records the heart rate and distance of the individual training sessions. These are given to both the IG and CG participants to exclude an effect on the study outcome only by wearing the smartwatch. Furthermore, group or partner training can bring motivational and social benefits [130-132], which is not directly provided in our web-based physical exercise training support. This may reduce adherence of the participants to the study and, additionally, exclude the social aspect of the effect of an active lifestyle on resilience. Therefore, communication via the web-based platform is intended to be frequent and without any restraints toward the trainer. Finally, inexperience, fear, and the risk of injury can occur during an unaccustomed and intensive training load, which could be reduced or not arise at all through presence support. To counteract this, we have implemented a 2-week adaptation phase in our training intervention that will offer an easy training start and reduce the indicated risks. In addition, we address the individual needs of the participants based on their weekly feedback, so overload is unlikely to occur during the intervention. Adhering to the described improvements in web-based physical exercise interventions will offer the most individual and effective training support with a simultaneously reduced workload for the coach. With this, our research group has already successfully conducted similar studies using the internet for training interventions in patients with Barrett carcinoma, nonalcoholic fatty liver disease, depression, cystic fibrosis, and systemic lupus erythematosus [40-45].

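### The only stated harm-recording rule covers the examination visits, not the 8 weeks of home running where the article itself sees injury risk

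*Protocol article*

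**What the plan says.** **The harm rule.** Data Management and Security contains the only sentence in the article on recording and reporting harms: "Any harm or unintended events during the examinations will be recorded", and such events go to the state medical association. The same paragraph adds a commitment that is not restricted to visits: "All dropouts and the reason for dropping out of the study will be reported".

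**The exposure.** Under Training Intervention, "an 8-week sports intervention will be carried out for the IG"; the control group does no training. Supervision is remote. Web-Based Supervision describes it as follows: "Although there is no face-to-face supervision, based on the objective training session heart rate data and GPS data as well as the subjective feedback", and says that this is adequate.

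**The acknowledged risk.** Strengths and Limitations says that "inexperience, fear, and the risk of injury can occur during an unaccustomed and intensive training load", and that face-to-face support might reduce this. The authors' answer is a 2-week adaptation phase and weekly adjustment.

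**Health information during training.** Intervention-group participants give weekly feedback, and in setting progression "The value for ailments has a higher priority than the load value". They also enter medical and sports values after each session and can message the coach about problems. The stated uses of the session entries are evaluation and adjustment of the next week's training.

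**Interim safety.** Results says that among the 31 completers (17 intervention, 14 control) "no serious adverse incidents were reported". The Abstract says the same.

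**The concern.** The intervention under test is a running programme for previously inactive adults, done away from the centre. If harms are recorded only when they occur at an examination, the record covers the treadmill tests, blood draws and stress tests but not the training. Site staff who follow the sentence exactly would have no instruction to log a running injury at home as a harm.

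There is a second, comparative problem. Channels through which a training injury might surface exist for the intervention group only. If those channels were later searched for harms, one arm would have been asked every week and the other not at all, so a difference in counts could reflect how often people were asked.

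At stake is any later statement on the safety or tolerability of the web-based programme. The VO2peak and saliva cortisol analyses do not depend on it.

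**Working it through.** The plan states no figure on this point, so the main check is to set the sections side by side. The arithmetic gives scale only.

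**1. What examination means.** Trial Design and Participants calls T0 and T1 the baseline examination and T2 and T3 the final examination, and places the training between T1 and T2. The harm rule uses the same word, so its natural scope is the four visits.

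**2. Does another sentence extend the scope?** No.
- Weekly ailment values (Training Intervention): used to set training progression.
- Session entries (Web-Based Supervision): used for evaluation and training adjustment.
- Message function (Web-Based Supervision): a contact route, with no stated recording rule.
- Dropout reasons (Data Management and Security): reported for all dropouts, but an injured participant who finishes is not captured.

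The information is therefore partly collected. What is missing is the link to the harm record.

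**3. Is ascertainment equal by arm?** The first three channels belong to the training and so to the intervention group. Under Training Intervention, the control group's smartwatch serves only to record daily activity. Both arms complete the SF-36 at T0 and T2, which touches on bodily pain and physical functioning over the past 4 weeks, but it is not a harm record and covers half of an 8-week period.

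**4. Exposure outside the rule.** Assuming 35 intervention participants (half of the target of 70): 35 × 8 = 280 person-weeks. For the 17 intervention completers so far: 17 × 8 = 136 person-weeks. These are amounts of exposure, not counts of lost events.

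**5. Denominator of the interim statement.**
- Included: 31 completed + 4 withdrew + 8 not yet started = 43, which matches Results.
- Started: 31 + 4 = 35. Dropout: 4/35 = 11.4%, which reproduces the article's rate.
- By arm, taking 17 and 14 as completers: 17 + 2 = 19 intervention and 14 + 2 = 16 control participants had started.
- Left out of the safety statement: 4 of 35 (2 per arm). Their reasons are described only as individual.

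**6. What zero events could show at best.** With complete capture, the one-sided 95% upper bound for 0 of n is 1 − 0.05^(1/n).
- 0 of 17: 1 − 0.05^(1/17) = 0.162, or 16.2%
- 0 of 31: 1 − 0.05^(1/31) = 0.092, or 9.2%

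These bounds follow from the sample size and would be the same under perfect recording. They do not measure this defect. They show only that the interim statement would be weak evidence even if ascertainment were complete.

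**The case against.** The best defence is that this is a journal article. The sentence says what happens to events at examinations; it does not say that other events go unrecorded, and the full protocol may define harms more widely. If the article were silent on scope, that would settle the matter. It is not silent: it states a scope, and that scope omits the exposure whose risk the article discusses. The defence limits the point to what is written here and does not remove it.

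Four stronger readings are tempting, and the documents do not support them.

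- *The training is unsupervised.* It is remotely supervised, with heart rate, GPS and weekly feedback; only face-to-face supervision is absent.
- *Home injuries would go unseen.* Ailment ratings, session entries, messages and dropout reasons could all bring them to light, and evaluation is a stated use of the session entries.
- *The interim statement is wrong, or covers visit days only.* Results sets no time window and does not refer to the harm rule. Serious incidents could have reached the team by the routes above. The fair criticism is that method and period are not given and that withdrawals are left out.
- *A comparison of harms between arms is impossible.* Both arms return at T2 and T3, both complete the SF-36, and withdrawals are already given by arm. The comparison would be unequal, not impossible.

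**Conclusion.** The point holds as a defect of scope and linkage. The single harm-recording rule, read as written, stops at the examinations and leaves the 8-week training period without a recording commitment. The information that exists for that period is tied to training, comes from one arm, and is not routed into the harm record. Separately, the interim statement has no stated ascertainment and rests on 31 of the 35 participants who had started.

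The scale is about 280 person-weeks of planned training outside the rule, and 4 of 35 starters (11.4%) outside the interim statement. The number of harms missed, if any, cannot be estimated from the article.

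The conclusion assumes that examination keeps the meaning given to it under Trial Design and Participants, that the target of 70 splits evenly, and that the full protocol has no wider rule. If it has one, the remedy reduces to bringing the article's sentence into line with it. The change is worth making before recruitment resumes, but it does not touch the primary outcome analyses.

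**What to change.** 1. Reword the harm sentence in Data Management and Security so that any harm or unintended event from T0 to T3, including during home training, is recorded in both arms and reported by arm for everyone who started.
2. State that the intervention group's weekly feedback and messages to the coach feed the harm record.
3. Ask both arms one short harm question at T2, identically worded and covering the time since T1. This gives the arms one source of equal quality; events known only from weekly feedback should be shown separately.
4. When the interim statement is next reported, give the method and period of ascertainment and include the 4 who withdrew.
5. Asking earlier completers in retrospect is optional. Such answers must be marked as retrospective and kept apart from prospective ones.

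**Cost.** No new visits are needed. Trial Design and Participants requires ethics approval of an amendment before implementation, and a new question in both arms changes conduct, so this is a small amendment and not an administrative correction. More minor events will be reported. Any retrospective answers will carry recall bias. Recruitment is paused, and if the target of 70 counts those who start, 70 − 35 = 35 participants could still be covered prospectively.
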